### Design

The CATALYST trial is an investigator-initiated randomized, blinded, multicentre clinical trial of selenium supplementation versus placebo in patients with AIT. The trial has a parallel-group design with 1:1 allocation to the experimental intervention group and the control intervention group (Figure 1). Participants will be recruited from four clinical trial sites in Denmark (Odense University Hospital, Rigshospitalet, Bispebjerg Hospital, and the Hospital of Southwest Denmark). The trial also includes a register-based follow-up during the trial and during a period after completion of the intervention.

**Figure 1 F1:**
[figure not shown]
Trial flow chart (adapted from the CONSORT statement 2010).

### Trial participants

All patients with a diagnosis of AIT who are referred to, or followed-up at, a participating clinical trial site will be considered for participation in this trial. In addition, clinical trial sites may invite participants based on local trial site patient data or advertise in local media or via patient organizations. Patients may enter the CATALYST trial if they comply with the inclusion and exclusion criteria.

#### **
*Inclusion criteria*
**

Age ≥18 years; diagnosis of AIT with serum TPO-Ab ≥ 100 IU/ml measured within the last 12 months; LT4 treatment based on an initial serum TSH ≥ 4.0 mU/l; and written informed consent.

#### **
*Exclusion criteria*
**

Previous diagnosis of toxic nodular goitre, Graves’ hyperthyroidism, postpartum thyroiditis or Graves’ orbitopathy; previous radioiodine therapy, ATD treatment or thyroid surgery; morbidity, rendering the participant unable to process patient-reported outcomes or receive intervention during the trial; immunomodulatory medication; other medication known to affect thyroid function; pregnancy, breastfeeding or planned pregnancy within the next 18 months; allergy towards any component in the selenium or the placebo tablets; intake of selenium supplementation >55 μg/day; inability to read or understand Danish; or lack of informed consent.

### Trial intervention

#### **
*Selenium*
**

In this trial, oral tablets of selenium-enriched yeast will be used. The experimental intervention will be 200 μg selenium per day, corresponding to two 100 μg tablets SelenoPrecise^®^ in a formulation registered as a dietary supplement and produced by Pharma Nord ApS, Vejle, Denmark.

#### **
*Placebo*
**

The control intervention will be two placebo tablets per day as inactive spray-dried baker’s yeast, comprising 250 mg yeast placebo, 80 mg cellulose, 65 mg dicalcium phosphate, and ≤5 mg other inactive ingredients. Tablets will be identical to the experimental intervention as regards size, appearance, taste, smell and solubility and will be produced by Pharma Nord ApS, Vejle, Denmark.

#### **
*The trial data management system (TDMS)*
**

Since the design will involve limited interaction between participants and trial personnel, a considerable part of the data collection, trial conduct, trial surveillance and timing, is handled by a trial data management system TDMS. This system, named PROgmatic, is described in detail in an independent publication [45]. It consists of a patient-survey interface, a trial-personnel interface, a system-integration interface and a program ‘motor’. The system features include secure web-based data entry; electronic case report forms (eCRFs); central participant registration and randomization; automated emails linking to electronic patient-reported outcomes; automated reminders to participants; automated notifications to trial personnel regarding booking of trial visits, safety and compliance alerts and monitoring of trial progress. It will be used for collecting outcome data, adverse events, and other study-relevant information; for timing of trial events, that is, time for patient-reported outcomes and trial visits; for identification of need for action (for example, contact to a participant); and for delivery of output to personnel or participants (for example, email notifications). In this way, the eCRFs are created by integration of patient-input, trial-personnel input and collection of electronic data regarding biochemical analyses (that is, blood-tests taken as part of the usual routine). All activities are automatically logged. The TDMS complies with the security policies of the participating hospitals and the Act on Processing of Personal Data, and is approved by the Danish Data Protection Agency.

#### **
*Randomization*
**

Randomization will be performed centrally by a consultant at the SAS Institute A/S (Copenhagen, Denmark). The allocation sequences will be computer-generated with varying block size, and will be kept unknown to the investigators. Randomization will be stratified by clinical trial site and LT4 treatment duration (<3 months or ≥3 months) and the allocation ratio of intervention and control will be 1:1.

#### **
*Informed consent procedure*
**

Potential participants include all patients with suspected AIT who receive LT4 and are identified at referral or visits to the outpatient clinics or via advertising, as previously described. When AIT is confirmed (serum TPO-Ab ≥ 100 IU/ml, measured within the last 12 months), the patient is invited to an information visit. This visit involves obtaining medical history and written informed consent, blood and urine sampling, and information about trial contact as well as randomization.

#### **
*Concomitant medication or treatment*
**

The trial interventions are given in addition to conventional LT4 treatment. Treatment of the hypothyroidism *per se* will take place at participating clinical trial sites, with LT4 treatment at all clinical trial sites aiming for a serum TSH level within reference ranges, as recommended in local clinical guidelines. Patients are normally followed with blood sampling every 1 to 3 months to adjust LT4 dosage according to TSH levels, as well as visits in the outpatient clinic every 3 to 6 months. Participants in the CATALYST trial will be followed with blood sampling during the trial period, as stated in local clinical guidelines. Participants are advised not to take selenium supplementation in addition to the intervention. A dose of selenium common in multivitamin tablets is, however, allowed and participants are instructed and informed about this upon trial entry, and in the written participant information. The participants’ consumption of additional selenium supplements will be monitored during the trial at specific time points.

#### **
*Monitoring participant adherence to intervention*
**

During the trial, participants self-report their adherence to the intervention at the trial visits (3 months and 12 months after randomization) by stating the number of days a week they take their tablets. Participants will also be instructed to bring remaining tablets and empty containers to the 12 month visit, where they will be counted and registered by an investigator or trial nurse.

#### **
*Discontinuation*
**

A participant who no longer wishes to participate in the trial can withdraw informed consent at any time without need of further explanation, with no consequence on the participant’s further treatment. To conduct intention-to-treat analyses, with as little ‘missing data’ as possible, the investigator may ask the participant which aspects of the trial he or she wishes to withdraw from. This could involve the trial intervention, participation in the remaining follow-up assessments, or use of already collected data in the data analyses. The investigators shall discontinue a participant from the trial intervention at any time, if the participant complies with any of the exclusion criteria during the intervention period or experiences intolerable adverse reactions. In both cases, the investigator or the treating physician shall, if possible, encourage the participant to continue with follow-up assessment and allow the use of already collected data in the analyses.

#### **
*Blinding*
**

Blinding will be maintained for all parties in the trial, throughout all aspects of the trial. Statistical analyses will be performed with the blinding intact, for example, the experimental intervention and control intervention group will be randomly coded as ‘A’ and ‘B’. Two conclusions will be drawn; one assuming that ‘A’ is the experimental intervention group and ‘B’ is the control intervention group, and one assuming the opposite. Only after this will the blinding be broken.

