Analyses will be performed using SAS (SAS Institute Inc. ©, Cary, NC, USA), version 9.3 or later. All analyses will be intention-to-treat analyses performed blinded with the two intervention groups concealed as, for example, ‘A’ and ‘B’. Significance tests will be at the 5% level and two-sided. Table 2 shows, for each outcome, its priority, when it will be measured, the mathematical type of measure, and the analytical procedure to be used when analyzing the outcome values. The analytical procedures and handling of missing values are described next.

**Table 2 T2:** Outcome measures

**Outcome (priority)**	**Times of measurements**	**Mathematical type of quantity (analytical category)**
ThyPRO composite scale score (P)	Time sequence of six measurements^a^	Numerical (1 + 2)
ThyPRO hypothyroid symptoms (S)	Time sequence of six measurements^a^	Numerical (1 + 2)
ThyPRO goitre symptoms (S)	Time sequence of six measurements^a^	Numerical (1 + 2)
LT4 dosage (S)	Time sequence of four measurements^b^	Numerical (1 + 2)
Serum TPO-Ab (S)	Time sequence of four measurements^b^	Numerical (1 + 2)
Serum FT3/FT4 Ratio (S)	Time sequence of four measurements^b^	Numerical (1 + 2)
Plasma selenium (S)	Time sequence of four measurements^b^	Numerical (1 + 2)
Biomarkers of immunology and oxidative stress (S)	Time sequence of four measurements^b^	Numerical (1 + 2)
Adverse reactions (S)	End of trial	Rate (3)
Serious adverse events (S)	End of trial	Rate (3)

Outcomes with priorities, times of measurement and mathematical types of quantity with analytical categories. P, primary outcome measure; S, secondary outcome measure. Analytical categories 1 to 3 are defined in the main text. ^a^, includes five measurements relative to the reference time (6 weeks, 3 months, 6 months, 12 months and 18 months after randomization); ^b^, includes three measurements relative to the reference time (3 months, 12 months and 18 months after randomization).

#### **
*Analytical procedures*
**

Depending on the specific analytical category of each outcome measure, one or two of three types of regression analyses will be applied (Table 2).

#### **
*Analytical categories*
**

*Type 1* includes a continuous outcome measure (*y*) measured 3 to 6 times at 6 weeks, 3, 6, 12 or 18 months after randomization. It is viewed as a linear function of time (*t*). The model is:

*y* = *a* + *b***I* + *c***t* + *d***I***t*

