Depending on the mean value structure in the two groups, this model may be enhanced to include a second- or third-degree polynomial. *I* is the intervention indicator, and *a*, *b*, *c* and *d* are the coefficients of the regression equation. A mixed model with repeated measures will be used. An unstructured covariance matrix will be used. In the case of lack of convergence, the following covariance structures will be tried in the specified order: the spatial power law and the compound symmetric.

*Type 2* includes a single continuous outcome measure. The general linear univariate model will be used. As a sensitivity analysis, a nonparametric test (Mann Whitney) will be conducted and the result discussed.

*Type 3* includes a count of events within a specified period of counting as outcome measure. The generalized linear model will be used with the Poisson distribution, link = log and log (period) as offset. As a sensitivity analysis a nonparametric test (Mann Whitney) is conducted to compare the distributions of rates between the groups and the result discussed.

#### **
*Missing values*
**

If the distributions of the primary outcome measure differ significantly between the two intervention groups, multiple imputations (MI) will be used to replace missing data with substituted values using SAS version 9.3 or later. In the MI analysis, the model variables and additional variables significantly related to the variables with missing values of these variables will be used. Ten imputed data sets will be produced.

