## Discussion

The data available from previous trials warrant further investigation, since a benefit from selenium supplementation is still unproven in patients with AIT. In previous trials of intervention with selenium in patients with AIT, effect on serum TPO-Ab concentration has been the primary outcome. Intervention durations of 3, 6, 9, and 12 months using different selenium formulations have shown positive effects on serum TPO-Ab concentrations. This trial will be the largest yet, with 472 participants, and the first to measure changes in quality of life, by ThyPRO, as the primary outcome. The sample size estimate does not take dropouts or off-trial use of selenium supplements into account. Plasma selenium concentrations will be measured to assess selenium intake during the trial. Importantly, utilizing the ThyPRO questionnaire will enable us to determine how selenium supplementation may affect specific aspects of thyroid-related quality of life in AIT patients. In assessing quality of life, the effect of levothyroxine alone will be taken into account by adjusting for TSH levels. Choosing a 12-month intervention period allows for a time sequence of five measurements. The 6-month postintervention follow-up period was added to assess sustained effects. This trial will also look into selenium’s mechanisms of action in AIT, by measuring biomarkers of immunological activity, and will be the first to evaluate whether selenium supplementation affects LT4 dosage. Dosage reduction is of clinical interest and discontinuation of LT4 would be of direct clinical relevance. An effect of selenium supplementation on LT4 dosage is conceivable, owing to upregulation of selenoproteins involved in thyroid hormone synthesis or thyrocyte protection.

Participants will be stratified for LT4 treatment duration of more or less than three months, corresponding to newly diagnosed and established patients, respectively. Participants in the newly diagnosed patient group will respond to LT4 treatment *per se*, in terms of restoration of euthyroidism, while the established patient group will not experience major fluctuation in the thyroid hormone levels during the study period. The stratification also allows an investigation of whether the newly diagnosed and established patient groups respond differently to selenium supplementation. This investigation will, however, be strictly exploratory, as it is likely to be underpowered.

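### The stratification factors (site, LT4 duration) are absent from the written-out primary model; the effect is conservative, costing some precision but not validity

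*Protocol article*

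**What the plan says.** Under Trial intervention, Randomization, the Protocol article states: "Randomization will be stratified by clinical trial site and LT4 treatment duration", with LT4 duration split at 3 months, and "the allocation ratio of intervention and control will be 1:1". With four sites this gives 4 × 2 = 8 strata.

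Under Statistical analyses, Analytical categories, the Type 1 model for repeated continuous outcomes is y = a + b·I + c·t + d·I·t, where I is the intervention indicator and t is time. Of the outcome it says: "It is viewed as a linear function of time". One extension is named: "this model may be enhanced to include a second- or third-degree polynomial". The covariance is also fixed: "An unstructured covariance matrix will be used", with two fallback structures. No stratification factor is named for Type 1, 2 or 3. Table 2 assigns the primary outcome to Types 1 and 2.

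The Discussion expects newly diagnosed patients to respond to LT4 itself, "while the established patient group will not experience major fluctuation in the thyroid hormone levels during the study period". It also says that "the effect of levothyroxine alone will be taken into account by adjusting for TSH levels", although TSH does not appear in the model equation. The section on expected recruitment plans half of the 472 participants from the group with less than 3 months of LT4.

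**The concern.** The plan balances the arms on two factors and then analyses the data as if allocation had been unrestricted. Stratified allocation removes between-stratum differences from the comparison of arms. A model without the strata still counts those differences as residual variance, so it reports a standard error larger than the true one.

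The plan's own reasoning makes LT4 duration likely to matter. Two equal halves of the trial are expected to follow different courses, yet the model fits one time curve per arm. A polynomial bends that curve but cannot separate the strata. At stake is precision: confidence intervals wider than necessary and some power given away. The Discussion also says that the sample size makes no allowance for dropout or off-trial selenium use.

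**Working it through.** **Inputs from the Protocol article** (Statistical analyses, sample size estimation): target difference 4 points, SD 20, within-participant correlation 0.50, five measurements with compound symmetry, two-sided α 0.05, power 80%, 236 per arm. Stratum shares are 50:50 (Expected participant recruitment).

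**Assumed, not in the document:** the difference D between the two LT4-duration strata in the averaged ThyPRO score. It is varied below. Follow-up is taken as complete, as in the plan.

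**Step 1. Reproduce the plan's figure.** Variance of the mean of five measurements: 400 × (1 + 4 × 0.5)/5 = 240. Sample size per arm: 2 × (1.960 + 0.842)² × 240/4² = 235.5, rounded up to 236. Power at 236 is 80.1%. The stated figure reproduces.

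**Step 2. Split the variance.** With equal strata, D²/4 of the 240 lies between strata. The model without strata uses SE_model = √(2 × 240/236) = 1.426. Under stratified allocation the true value is SE_true = √(2 × (240 − D²/4)/236).

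**Step 3. Operating characteristics.**
- True type I error of the unadjusted test: 2 × [1 − Φ(1.96 × SE_model/SE_true)]
- Power, unadjusted: Φ[(4 − 1.96 × SE_model)/SE_true]
- Power, strata in the model: Φ(4/SE_true − 1.96)

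| Assumed D | SE_true | SE_model/SE_true | Type I error, unadjusted | Power, unadjusted | Power, adjusted | n per arm for 80%, adjusted |
|---|---|---|---|---|---|---|
| 0 | 1.426 | 1.000 | 5.00% | 80.1% | 80.1% | 236 |
| 4 | 1.414 | 1.008 | 4.81% | 80.3% | 80.7% | 232 |
| 8 | 1.378 | 1.035 | 4.25% | 80.9% | 82.7% | 220 |
| 10 | 1.350 | 1.057 | 3.84% | 81.4% | 84.2% | 211 |
| 12 | 1.315 | 1.085 | 3.35% | 82.0% | 86.0% | 201 |

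The power forgone is about 0.5, 2 and 4 percentage points at D = 4, 8 and 12.

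**Step 4. Simulation** (8 equal strata, assumed blocks of 4 and 6, 4,000 runs per setting). At D = 10, type I error was 3.7% unadjusted and 5.2% adjusted, and power was 81.3% and 84.2%. At D = 5 the difference in type I error (5.4% against 5.6%) is within simulation error, since √(0.05 × 0.95/4000) is about 0.35 percentage points.

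**Step 5. Sensitivity to the meaning of the SD.** Steps 2 and 3 take 20 as the SD across both strata together. If it were the SD within a stratum, adjusted power would be 80.1% for any D. At D = 8, SE_model would be √(2 × 256/236) = 1.473 and unadjusted power Φ[(4 − 1.96 × 1.473)/1.426] = Φ(0.78) = 78.2%. The loss is again about 2 points, but the unadjusted figure is then below 80%.

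**Limit.** All this concerns the average over measurements. A constant gap between strata cancels from a slope. For the coefficient d, only a difference in slope between strata matters, and the document gives nothing from which to estimate it.

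**The case against.** The strongest objection is scope. The article condenses a longer protocol, an analysis plan may list covariates, and the Type 1 equation is a template serving eight rows of Table 2. The Discussion's TSH adjustment shows that the equation is not an exhaustive list. Part of this stands: the article never says that the strata will be left out, and a fuller plan may include them. But the article prints the equation, its one named extension and the order of covariance fallbacks. A model specified that closely without the randomisation factors can fairly be questioned. TSH does not fill the gap. It is not a stratification factor, it is measured at baseline and later, and the article does not say which value is meant.

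The second objection is size, and it stands. Gaps of 8 to 12 points are two to three times the target effect and have no source in the document. At 4 points the gain is trivial.

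Three stronger readings are tempting and are not supported:
- **That inference is invalid.** The error runs only in the conservative direction.
- **That LT4 duration is the strongest known source of outcome variation.** The document ranks no sources and gives no ThyPRO difference between strata. It only implies that duration is prognostic.
- **That omitting the strata leaves the trial underpowered.** The 236 per arm reproduces without any stratum adjustment. Averaging four measurements instead of five gives 78.5% power even at D = 0, but that shortfall comes from the number of measurements, not from the strata.

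**Conclusion.** The point holds as a moderate matter of efficiency. The Type 1 model, as written, omits both stratification factors, one of which the Discussion itself expects to shape the course of the outcome. The consequence is standard errors about 1% too large at an assumed 4-point gap, 3 to 4% at 8 and 8 to 9% at 12, with true type I error between 4.8% and 3.4% and the power losses shown above. There is no bias and no type I inflation.

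The omission itself is certain from the text; its size is not. The figures rest on an assumed constant gap, equal strata, the average of five measurements and complete follow-up. That 80% power is still met also requires reading the SD of 20 as that of the whole population. The loss for the intervention-by-time term remains unknown.

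**What to change.** - **Type 1:** add site, LT4-duration stratum (below 3 months, or 3 months and over) and stratum-by-time as fixed effects. Use the same time terms as the rest of the model: linear, or the polynomial if one is adopted. A stratum-by-visit factor would not fit a model that treats time as continuous.
- **Type 2:** add site and stratum.
- **Type 3:** add site and stratum only where event counts allow, since sparse counts by site would be poorly estimated.
- **TSH:** reconcile the Discussion with the model equation. State whether TSH enters, in which analyses, and which measurement is used. A value taken after randomisation may itself be affected by the intervention.

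For Type 1 the cost is 3 parameters for site, 1 for stratum and 1 to 3 for stratum-by-time, so 5 to 7 in all with 472 participants. The trial data management system already uses site and LT4 duration to deliver randomisation numbers, so no new data are needed. The sample size does not change.

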### Safety

The selected dosage and the exclusion criterion regarding additional selenium supplementation intake ensure that participants have a total selenium intake of less than 300 μg per day, as recommended in current European guidelines on tolerable upper intake level [46]. It has previously been concluded that SelenoPrecise^®^ is adequately characterized, of reproducible quality, and that there is no evidence of toxicity even at intake levels far above 300 μg per day [47]. In a randomized clinical trial (UK PRECISE) with 501 volunteer participants from general practice, mean plasma selenium increased from 88.1 μg/l to 188.1 μg/l following 6 months supplementation with 200 μg/day SelenoPrecise [48]. While no serious adverse events occurred, 12 adverse events were reported, primarily stomach or abdominal discomfort, which were equally distributed between the selenium and placebo groups [48]. The tablets used were identical to the planned experimental intervention agent in CATALYST, and CATALYST participants are expected to be very similar to the UK PRECISE participants, with regard to baseline selenium status.

The safety profile of the dietary supplement used in the CATALYST trial is based on the summary of product characteristics (SPC) for the drug formulation of SelenoPrecise^®^ from the Danish Medicines Agency. Common adverse reactions (between 1/10 and 1/100) are complaints from the gastrointestinal system, while uncommon (between 1/100 and 1/1,000) and rare (between 1/1,000 and 1/10,000) adverse reactions are mainly of a dermatological nature.

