### Outcomes

Data will be collected for outcome assessment at six specified times during the trial (Table 1).

**Table 1 T1:** Timing of data collection

**Variable**	**Inclusion baseline**	**Follow-up 6 weeks ± 1 week**	**Follow-up 3 months ± 2 weeks**	**Follow-up 6 months ± 2 weeks**	**Follow-up 12 months ± 2 weeks**	**Follow-up 18 months ± 2 weeks**
Visit	*x*		*x*		*x*	*x*
Weight	*x*_ *v* _		*x*_ *v* _		*x*_ *v* _	*x*_ *v* _
Medical treatment	*x*_ *v* _		*x*_ *v* _		*x*_ *v* _	*x*_ *v* _
ThyPRO	*x*_ *r* _	*x*_ *r* _	*x*_ *r* _	*x*_ *r* _	*x*_ *r* _	*x*_ *r* _
TSH, FT4, FT3	*x*_ *s* _		*x*_ *s* _		*x*_ *s* _	*x*_ *s* _
TPO-Ab	*x*_ *s* _		*x*_ *s* _		*x*_ *s* _	*x*_ *s,* _
LT4 dosage	*x*_ *v* _		*x*_ *v* _		*x*_ *v* _	*x*_ *v* _
Immunological and oxidative stress biomarkers	*x*_ *s* _		*x*_ *s* _		*x*_ *s* _	*x*_ *s* _
Selenium	*x*_ *s* _		*x*_ *s* _		*x*_ *s* _	*x*_ *s* _
Creatinine/iodine ratio in spot urine	*x*_ *s* _					
Tablet count			*x*_ *v* _		*x*_ *v* _	
Consumption of additional selenium	*x*_ *v* _		*x*_ *v* _		*x*_ *v* _	*x*_ *v* _
Adverse reactions			*x*_ *v* _		*x*_ *v* _	*x*_ *v* _
Serious adverse reactions and events (SARs, SUSARs and SAEs)						*x*_ *p* _

All assessments must be made at the time points specified above. If not possible at the specified time, the assessment shall still be conducted, and the time of assessment shall be noted in the specified electronic case report form (eCRF). *x*_
*v*
_, analyzed via data obtained in eCRFs at trial visits, administered through the trial data management system (TDMS); *x*_
*r*
_, analyzed via patient-reported outcomes, administered through the TDMS; *x*_
*s*
_, analyzed in blood or urine samples obtained at trial visits; *x*_
*p*
_, analyzed via public national registries at the end of the trial.

#### **
*Primary outcome*
**

Improved thyroid-related quality of life during the 12 months intervention after randomization, as measured by one composite score from the ThyPRO questionnaire [49].

#### **
*Secondary outcomes*
**

Secondary outcome assessment is specified in Table 1. Forkhead Box P3 mRNA will be measured as an immunological biomarker, and urinary 8-oxo-2'-deoxyguanosine and 8-oxoguanine will be measured as oxidative stress biomarkers.

#### **
*Assessment of adverse reactions and events*
**

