The latest version of the SPC shall at all times be used for the assessment of adverse reactions (ARs), which will be reported as a secondary trial outcome. Participants are questioned about ARs according to Table 1. In addition, participants are instructed to contact their trial contact person if they experience symptoms suggestive of ARs.

In the assessment and reporting of serious adverse reactions (SARs), serious unexpected serious adverse reaction (SUSARs) and serious adverse events (SAEs), data on hospital admissions and mortality will be obtained through national registries at the end of the trial. Also, participants are informed and instructed to contact their trial contact person if they are admitted to a hospital for selenium intoxication, experience a clinical picture indicative of selenium intoxication, or experience a clinical picture that is unexpected but suspected to be related to selenium intoxication. When a possible serious event (SAE, SAR or SUSAR) is identified, details will be sought from the patient’s medical record and through direct contact with the patient. Any SAE, SAR or SUSAR will be reported as an outcome measure.

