It is of major importance to the CATALYST trial’s initiators that the results will be as directly applicable to daily clinical practice as possible. Therefore, it will be conducted as a pragmatic trial [52], with participating patients following their usual treatment at their usual hospitals in the care of whichever physician is involved. At the same time, it is a priority to collect high-quality data with respect to HRQL, since this is the primary outcome of the trial.

The intent of conducting a pragmatic trial, while still measuring HRQL meticulously, presents a challenge. Considerable effort has therefore been directed at designing a trial data management system that can handle distance from participants and maintain close monitoring [45]. The system initiates and keeps track of patient-reported outcomes and identifies a need for trial personnel input and action. The system also identifies the site of the information provider and LT4 treatment duration of new participants, in order to deliver randomization numbers. Meticulous follow-up of missing responses to the HRQL measurements is incorporated into the system, to minimize the well-known problem with missing HRQL data in clinical trials.

The intent to comply with the ICH-GCP guidelines is also a challenge when conducting a pragmatic trial. In the CATALYST trial, the experimental intervention is a dietary supplement rather than a drug. The need to monitor adverse reactions and events is addressed by a combination of thorough instruction of the participants to contact their trial person in case of symptoms indicative of adverse reactions or events, surveillance of patients’ responses to prompts through the trial data management system and integration with national databases regarding hospitalizations.

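### Cheap improvement (minor): during treatment, Table 1 asks about medical treatment, additional selenium and adverse reactions only at months 3 and 12; asking also at the existing 6-month electronic contact would shorten the longest interval from 9 to 6 months.

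*Protocol article*

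**What the plan says.** **The duty.** Under Trial intervention, Discontinuation, investigators must take a participant off the tablets at any time "if the participant complies with any of the exclusion criteria during the intervention period", or if adverse reactions become intolerable. Two exclusion criteria that can arise after entry concern items in Table 1: excluded medication (immunomodulatory or affecting thyroid function) and selenium supplements above 55 μg/day.

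**The schedule.** Outcomes, Table 1 marks medical treatment and additional selenium at baseline and months 3, 12 and 18, and adverse reactions at months 3, 12 and 18. All three are coded as items collected at trial visits. There is no visit at 6 weeks or 6 months, where ThyPRO, sent electronically, is the only entry. The table note says "All assessments must be made at the time points specified above", and it has late assessments done anyway and their time recorded.

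**The text ties these items to the schedule.** On adverse reactions: "Participants are questioned about ARs according to Table 1" (Outcomes, Assessment of adverse reactions and events). On supplements: "consumption of additional selenium supplements will be monitored during the trial at specific time points" (Trial intervention, Concomitant medication or treatment).

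**Other routes.** Participants are told to call their trial contact about suspected adverse reactions. At entry and in writing they are advised against extra selenium beyond a usual multivitamin dose. The trial data management system provides "automated notifications to trial personnel regarding booking of trial visits, safety and compliance alerts and monitoring of trial progress". The Discussion adds surveillance of "responses to prompts through the trial data management system and integration with national databases regarding hospitalizations". Usual care at the trial sites continues: "Patients are normally followed with blood sampling every 1 to 3 months to adjust LT4 dosage according to TSH levels", with clinic visits every 3 to 6 months.

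**The concern.** The stopping rule applies throughout the 12 months of tablets, but the scheduled questions that would bring its triggers to light are bunched at the start and the end. The month-12 answer arrives as treatment finishes and the month-18 answer comes six months later. Neither can usefully shorten exposure.

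Two things are at stake, both modest.

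- **Stopping in time.** If an excluded medicine or a supplement above the cap is started after month 3, its discovery before month 12 depends on unscheduled routes or on system prompts whose items and timing the article does not give. The Safety section says that the dose and "the exclusion criterion regarding additional selenium supplementation intake ensure that participants have a total selenium intake of less than 300" μg per day. That assurance depends on the supplement cap holding during treatment, and the cap is re-asked by a scheduled question only once while tablets can still be stopped.
- **Adverse reactions as an outcome.** Table 2 lists adverse reactions as a secondary outcome analysed as a rate. Reactions that are neither called in nor caught by a prompt must be remembered at month 12 over most of the treatment year.

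**Working it through.** The plan gives no figure for this interval, so there is none to reproduce. The sample size of 236 per group does not depend on the point.

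**1. Table 1, row by row, within the treatment period**

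| Item | Baseline | 6 wk | 3 mo | 6 mo | 12 mo |
|---|---|---|---|---|---|
| Trial visit | yes | – | yes | – | yes |
| Medical treatment | yes | – | yes | – | yes |
| Additional selenium | yes | – | yes | – | yes |
| Adverse reactions | – | – | yes | – | yes |
| ThyPRO (electronic) | yes | yes | yes | yes | yes |

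After baseline, month 3 is the only marked time before tablets end.

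**2. Longest interval now.** The windows at months 3 and 12 are ±2 weeks, and 2 weeks = 14/30.44 = 0.46 month.
- Nominal: 12 − 3 = 9 months, or 9/12 = 75% of the treatment period.
- Shortest: (12 − 0.46) − (3 + 0.46) = 8.1 months.
- Longest: (12 + 0.46) − (3 − 0.46) = 9.9 months.

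**3. Longest interval with the items added at month 6** (also ±2 weeks).
- Months 3 to 6: 3 months. Months 6 to 12: 6 months.
- Longest interval: 6 months nominal, from 6 − 0.92 = 5.1 to 6 + 0.92 = 6.9.
- Adding 6 weeks as well splits the first 3 months but leaves the longest interval at 6, so it is optional.

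**4. Usual-care contacts strictly between months 3 and 12**, counting from randomization at the frequencies in Concomitant medication or treatment.
- Clinic visits: every 3 months gives months 6 and 9 (2); every 6 months gives month 6 (1).
- Blood samples: monthly gives months 4 to 11 (8); every 3 months gives months 6 and 9 (2).

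The interval therefore contains patient contact. What it lacks is a scheduled trial question on these items. The stated purpose of the blood samples is LT4 adjustment by TSH. Plasma selenium is no backstop, because Table 1 draws it at the same visits.

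**5. Room under the 300 μg limit.** 200 (tablets) + 55 (permitted supplement) = 255, which leaves 45 μg/day for diet. The article gives recommended daily intakes of 50 μg for men and 40 μg for women but no actual dietary intake. This shows only that the cap matters to the assurance. It does not show that anyone would exceed the limit.

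**The case against.** The strongest reply is that nothing here is wrong. The Discontinuation section sets a duty to act once a trigger is known and prescribes no screening frequency. Table 1 is introduced as a timetable for outcome data. Limited contact is a deliberate feature of a pragmatic design, and the article describes several other ways for a trigger to surface. Site clinicians see participants every 3 to 6 months, and the article involves the treating physician when a participant is discontinued. Supplement use is also addressed by prevention, through advice at entry. The data management system is described in full in a separate publication not at hand, so part of the remedy may already exist.

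Most of this stands, and it limits the point to an improvement. What it does not remove is that the article itself ties adverse-reaction questioning to Table 1 and supplement monitoring to set times. The 9-month interval is therefore a stated schedule and not an omission caused by condensing. It is also fair to ask why 6 months is adequate if 9 is not. No threshold is claimed; month 6 is chosen because a contact already exists there.

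Three stronger readings are tempting and unsupported:

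- **That the duty to stop cannot be met between months 3 and 12.** The other routes also serve it.
- **That pregnancy goes unchecked.** An outcome table in a condensed article need not list pregnancy procedures, alert rules or full participant instructions; the full protocol may hold them.
- **That participants are harmed or the ThyPRO result is biased.** The Safety section reports no evidence of toxicity at intakes far above 300 μg/day, and nothing links this schedule to bias in the primary outcome. The article also gives no event rates or onset times from which to estimate missed or delayed triggers.

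**Conclusion.** The point holds as a minor, low-cost improvement. Scheduled trial questions on medical treatment, additional selenium and adverse reactions leave 9 of the 12 treatment months uncovered between month 3 and month 12 (8.1 to 9.9 months with windows). Month 3 is the only scheduled check after baseline that can still lead to earlier stopping, and adverse reactions not reported by another route face a recall period of the same length.

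This rests on reading Table 1 as printed and on the two statements that tie questioning to set times. It also assumes that no system prompt already asks these items in between; the article neither says nor excludes this. The expected gain is somewhat earlier detection and better recall of non-serious reactions. Sample size, power and the primary analysis are unaffected.

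**What to change.** In Table 1, mark medical treatment, additional selenium and adverse reactions as patient-reported items in the 6-month column, and optionally in the 6-week column. Send them as a short block that opens only after ThyPRO has been completed, so that symptom questions cannot influence the primary-outcome answers. Set the data management system to alert the trial contact person on any positive answer, who then decides under the existing stopping rule. The stopping criteria do not change.

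The cost is a few questions on a contact that already takes place, one alert rule in a system that already issues alerts, slightly more participant burden and a few follow-up calls. No visit, blood sample or additional participant is needed.
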